## Abstract

The role of psychological factors in the pathophysiology and treatment of chronic visceral pain in disorders of gut-brain interactions (DGBI) is increasingly appreciated. Placebo research has underscored that expectations arising from the psychosocial treatment context and from prior experiences shape treatment responses. However, effects of negative expectations, i.e., nocebo effects, as they are likely crucial elements of DGBI patients’ clinical reality, have thus far only rarely been investigated in the context of visceral pain, with untapped potential for improved prevention and treatment. The experimental randomized-controlled pain study “NoVis,” carried out within the Collaborative Research Center (CRC) 289 (“Treatment Expectation”), aims to close gaps regarding the generation and persistence of nocebo effects in healthy volunteers. It is designed to elucidate effects of negative expectations in a multiple-threat paradigm with intensity-matched rectal distensions and cutaneous thermal stimuli, allowing to test nocebo effects in the visceral and somatic pain modalities. Negative expectations are experimentally induced by elements of doctor-patient communication (i.e., instruction) and/or by surreptitious amplification of symptom intensity (i.e., experience/learning) within a treatment context. Accordingly, the repeated measures between-subject design contains the between-group factors “treatment instruction” (negative vs. control) and “treatment experience” (negative vs. control), with volunteers randomized into four experimental groups undergoing several pain stimulation phases (repeated factor). This allows to compare the efficacy of instruction vs. experience, and more importantly, their combined effects on the magnitude of negative expectations and their impact on pain responses, which we expect will be greatest for the visceral modality. After a *Baseline*, short-term effects are assessed during a test phase accomplished on study day 1 (*Test-1 Phase*). To explore the persistence of effects, a second test phase is accomplished 1 week later (*Test-2 Phase*). Effects of negative expectations within and across pain modalities are assessed at the subjective and objective levels, with a focus on psychophysiological and neuroendocrine measures related to stress, fear, and anxiety. Since nocebo effects can play a considerable role in the generation, maintenance, or worsening of chronic visceral pain, and may even constitute risk factors for treatment failure, knowledge from experimental nocebo research has potential to improve treatment outcomes in DGBI and other clinical conditions associated with chronic visceral pain.

## Introduction

1.

Chronic visceral pain is an important yet often underestimated clinical and societal problem not only in European countries like Germany (1) but worldwide (2, 3). From a clinical perspective, chronic or recurring pain arising from the viscera is highly prevalent, causes enormous suffering and significant healthcare expenditures (4). Effective treatment is notoriously difficult, especially in the absence of identifiable organic pathology, as is characteristic of functional gastrointestinal disorders such as the irritable bowel syndrome (IBS) and functional dyspepsia (FD) (5, 6). Since these conditions demonstrably involve alterations in gut-brain signaling, they are now based on international expert consensus referred to as disorders of gut-brain interactions (DGBI) (7). Treatment challenges are owed at least in part to the multifactorial etiology of DGBI involving biological, psychological, and social factors, embedded within a biopsychosocial model (8). Although the pathophysiology remains incompletely understood, it is assumed to involve visceral hypersensitivity and interoceptive hypervigilance, resulting from disturbances of the microbiome-gut-brain axis. Hence, from a mechanistic perspective, the complexity of the microbiome-gut-brain axis with its multitude of afferent and efferent pathways that connect the enteric nervous system and microbiome of the gastrointestinal (GI) tract with the central nervous system (CNS) poses research challenges to be resolved as a basis for improved treatment. One research target with great potential for successful translation into patient care is the brain as the organ where visceral signals are perceived as painful yet can also be modulated by psychological factors that can inform behavioral treatment approaches.

Psychological factors, including cognitions and emotions, modulate GI sensorimotor functions and illness behaviors, and thereby fundamentally contribute to the etiology, pathophysiology, and treatment of chronic visceral pain in DGBI. This is exemplified by long-standing research on the role of stress and stress mediators in visceral hyperalgesia (5, 9, 10), as well as by more recent work into interoceptive fear underlying hypervigilance and maladaptive avoidance (11). These psychological research lines have advanced mechanistic knowledge and paved the way toward translation into clinical application. Indeed, cognitive-behavioral treatment concepts targeting visceral pain are increasingly appreciated, continuously refined and more broadly disseminated (12, 13). Despite these impressive examples for successful translation from mechanistic studies in animals and humans into patient care, the potential of psychological concepts together with research tools from the cognitive and affective neurosciences is far from exhausted. At the interface of neurogastroenterology, the pain field and the cognitive neurosciences, transdisciplinary research into placebo and nocebo effects in visceral pain has great potential to advance mechanistic knowledge and improve treatment options for patients with chronic visceral pain (1, 5).

Placebo and nocebo effects demonstrably shape treatment outcomes, including patient-reported pain. They are mediated by treatment expectations arising from prior treatment experience as well as from communication and information provided by healthcare professionals, the media, or peers within any given psychosocial treatment context. Existing knowledge regarding treatment expectancy effects in chronic visceral pain comes primarily from studies conducted in the context of DGBI (1) as well as of chronic-inflammatory bowel diseases (14). High placebo response rates in clinical trials have initially drawn rather negative attention as a “nuisance” hampering successful drug development for treatment of pain-related gastrointestinal conditions (1, 15). Yet, it was also in patients with IBS that early brain imaging studies on the neural mechanisms underlying visceral placebo analgesia have been accomplished (16–18), paving the way for mechanistic work in other pain models and chronic pain conditions. In parallel to evolvement of research efforts and tools to study the placebo effect, treatment approaches built on positive treatment expectations (“placebo interventions”) have been successfully employed in IBS (19–21), inspiring efforts to utilize positive expectancy effects in the treatment of patients with other acute or chronic pain conditions [e.g., (22–25)]; and to further conceptual work on their role in psychotherapy (26).

Nocebo effects, mediated by negative expectations, remain less well-understood, although their scientific and clinical relevance undoubtedly rivals that of the placebo effect. In patients with DGBI, negative expectations and treatment-related worries and fears must be viewed as a part of the clinical treatment reality. The experience of sudden symptom aggravation as part of the typical waxing and waning of symptoms, worries about treatment choices and their possible side effects, and even repeated treatment failures are examples of how negative expectations could be generated and maintained in patients’ clinical reality. Such experiences shape cognitive and emotional responses, increasing maladaptive coping, catastrophizing, GI-specific fear and anxiety, and chronic stress burden. Together, these factors can contribute to visceral hyperalgesia and interoceptive hypervigilance as key mechanisms underlying the transition from acute to chronic visceral pain in patients. Hence, nocebo effects may play a considerable role in the generation, maintenance, or worsening of chronic gastrointestinal symptoms, and could even constitute risk factors for treatment failure (27). Given broad implications for the overlapping fields of gastroenterology, psychosomatic medicine, and pain (1, 28), elucidating nocebo effects in visceral pain in laboratory settings is necessary as a basis for enhancing knowledge about underlying psychological and neurobiological mechanisms. Given evidence supporting distinct differences between visceral and somatic pain in terms of perceptual and emotional responses as well as to neural processing (29–31), dedicated research in clinically relevant visceral pain models is needed in order to complement and extend nocebo knowledge from the somatic pain field.

Building on long-standing knowledge on the role of nocebo mechanisms in the generation and worsening of nausea [reviewed in (1)], our group started experimental work to systematically study both placebo and nocebo effects in visceral pain and fecal urgency induced by rectal distension [reviewed in (27)]. Together, data from behavioral and neuroimaging studies in healthy volunteers as well as in patients with IBS and IBD support that treatment expectations effectively change the subjective response to objectively identical painful visceral stimuli in healthy individuals, inducing placebo analgesia or nocebo hyperalgesia, along with changes in neural activation in key brain regions (32–34) known to be involved in the processing of visceral pain (35). While this research focused primarily on positive treatment expectations underlying placebo effects, we also initiated work elucidating the effects of negative treatment expectations, employing negative treatment suggestions and (thus far to a much smaller extent) learning/conditioning procedures to induce negative expectations underlying nocebo effects. Providing specific written and verbal treatment information or creating distinct treatment experiences through learning/conditioning procedures constitute the two paradigms which have been implemented in order to experimentally generate and explore both placebo and nocebo effects in laboratory settings (36, 37). The distinction between “instruction” and “experience/conditioning” as principle psychological mechanisms has been the basis for different experimental study designs, although it is becoming increasingly clear that these processes are conceptually and clinically intertwined (27). Clearly, prior experience and learning processes shape and interact with treatment instruction within any given clinical or experimental context, giving rise to expectancies (38). The combination of instruction and experience has been shown to be particularly effective in eliciting a nocebo effect (39), but this has never been tested in the context of visceral pain. The putative relevance of stress-related state factors like anxiety, fear, and stress also remains unclear in the context of nocebo effects but is strongly supported by our study showing that acute psychosocial stress amplified visceral nocebo effects in healthy individuals (40). Given that visceral pain sensitivity is demonstrably more responsive to the acute stress mediator cortisol (31) and uniquely driven by pain-related fear (29) it is intriguing to speculate that nocebo effects may be more pronounced for sensations arising from the visceral modality, as interoceptive sensations, when compared to exteroceptive sensations like thermal cutaneous pain. The notion of more “powerful” visceral pain modulation by mechanisms engaged during nocebo responses is also of interest given altered visceral pain-related fear learning in IBS (28) as well as greater emotional and hypothalamic–pituitary–adrenal (HPA) axis stress responsivity in patients with IBS and IBD (10). Therefore, elucidating the role of fear, anxiety, and stress in the context of nocebo research is a timely and important goal of our experimental study concept and design.

We designed an experimental randomized-controlled study dedicated to elucidating the effects of negative treatment expectations on subjective and objective responses to acute pain stimuli in healthy volunteers. The design allows to test the effects of negative expectations, generated by negative treatment instructions as well as by negative treatment experience separately, and more importantly, allows to elucidate their putative interaction. Within a “multiple-threat paradigm,” visceral pain is induced by pressure-controlled rectal distensions, delivered as part of a pain stimulation series also containing intensity-matched thermal cutaneous stimuli (41), modeling symptom burden in patients with multiple comorbidities and allowing us to elucidate specificity to pain modality. Effects of negative expectations on pain intensity and pain unpleasantness are assessed as primary outcomes. As secondary outcomes, different measures related to fear and stress are measured using behavioral, neuroendocrine, and psychophysiological responses. To elucidate the persistence of nocebo effects over time, participants are re-exposed to pain stimuli 1 week later.

The specific aims are as follows:

*Aim 1*: To test dynamic changes in treatment- and pain-related expectations within and outside of the psychosocial treatment context, i.e., on study days 1 and 2, as mediators of nocebo effects.

*Aim 2*: To test the effects of negative treatment expectations induced by instruction and/or experience on subjective and objective responses to acute visceral and somatic pain stimuli.

*Aim 3*: To determine if a negative treatment experience enhances the magnitude of negative instruction effects.

*Aim 4*: To compare the magnitude of nocebo effects in the visceral versus the somatic pain modality.

*Aim 5*: To assess the persistence of nocebo effects on responses evoked by a re-exposure to pain stimuli 1 week later.

*Aim 6*: To identify predictors of interindividual variability in the magnitude of nocebo effects and to elucidate associations with state and trait variables relevant to stress, anxiety, and fear at the behavioral, psychophysiological, and neuroendocrine levels.

## Methods

2.

### Setting, recruitment, and sample

2.1.

This ongoing study is conducted at the University Hospital Essen, University of Duisburg-Essen, Germany, as part of the Collaborative Research Center (CRC) 289 “Treatment Expectation”, funded by the German Research Foundation (Deutsche Forschungsgemeinschaft, DFG). The overall goal of the CRC is to elucidate mechanisms and clinical implications of treatment expectations.^1^ Within the ongoing first funding phase (7/2020–6/2024), research goals are primarily focused on health outcomes relevant to patients with chronic pain and depression. The present study is accomplished as part of subproject A04 (PI: author [name]), which addresses expectancy effects on pain with a unique focus on visceral pain and conditions involving the gut-brain axis. Ethical approval for research within subproject A04, including the present experimental study, was obtained from the ethics committee at University Hospital Essen (19-8897-BO). The study has been registered in the German Registry for Clinical Studies (DRKS: DRKS00024410). All participants sign consent (for details on two versions of consent forms, see section 2.4.3), and receive a financial compensation for their participation, comprising the two study days involving pain testing described herein, as well as additional assessments accomplished as part of the CRC’s central projects (see section 2.5.7).

The recruitment goal is to include a total of *N* = 120 healthy participants in the study. The sample size is based on *a priori* power analysis with G*Power (42) for interaction effects in a repeated measure ANOVA with the factors time and group. Assuming an effect size of *d* = 0.4 for interaction effects, *α* = 0.05, and 1-β = 0.90, the number of volunteers is *N* = 96. To account for possible exclusions or drop-out and to allow stratified recruitment of male and female volunteers, a group size of *N* = 30 subjects per final experimental group is intended.

To this end, healthy men and women between 18 and 45 years of age and a body mass index between 18 and 30 are recruited for a study on visceral vs. somatic pain perception by public advertisement in the surrounding universities, clinics, and community of the Ruhr area. The standardized recruitment and screening process consists of a structured telephone screening and a personal interview. Exclusion criteria include any acute or chronic health condition, with particular attention to recurring pain and frequent gastrointestinal symptoms based on self-report and an established questionnaire assessing various symptoms over the past 3 months (43), regular use of medications (except contraceptives and thyroid medication), elevated anxiety and depression scores based on the Hospital Anxiety and Depression Scale (HADS) (44)(subscale scores ≥8 used as cut-offs), pregnancy or breastfeeding (urinary pregnancy test on the first day of the study), and insufficient proficiency in the German language. A physical examination including a digital rectal examination is performed to exclude external or internal anorectal tissue damage which may interfere with rectal balloon placement. Given standardized brain scanning protocols accomplished as part of a CRC central project, the standard magnetic resonance imaging (MRI)-related exclusion criteria apply (e.g., metal implants, pacemaker, large tattoo in head/neck position, and known claustrophobia), and structural brain abnormalities are excluded in collaboration with the Institute of Diagnostic and Interventional Radiology and Neuroradiology. Given the study aims, especially the putative role of prior experiences with the experimental paradigms, any participation in an experimental pain study involving somatic or visceral pain stimuli within the previous 3 months (based on self-report) is also exclusionary.

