### Design and outcomes

2.2.

The study design is visualized in Figure 1, and procedures are described in detail in subsequent sections. The overall idea behind the design is to experimentally create negative treatment expectations through instruction and experience within a treatment context. This is reflected by the key elements of the repeated measures between-subject design containing the between-group factors “treatment instruction” (negative vs. control instruction) and “treatment experience” (negative vs. control experience). To assess the impact of experimental manipulations on outcome measures, subjective and objective responses to a series of visceral and somatic pain stimuli, delivered during several pain stimulation phases, are assessed (repeated factor). Healthy volunteers are randomized into four experimental groups (recruitment goal: *N* = 30 per group). On study day 1, pain thresholding and calibration/matching procedures and a brief pain habituation phase are initially accomplished. This is done to identify individual stimulation intensities for the pain stimulation phases. Several pain stimulation phases are subsequently accomplished (i.e., three on study day 1; one on study day 2), all consisting of a series of individually-calibrated rectal and thermal pain stimuli. After a *Baseline Phase*, all participants receive an i.v. catheter as a salient element of the psychosocial treatment context, with distinct treatment instructions. Briefly, the negative treatment instruction groups are informed that the opioid antagonist naloxone, which amplifies pain, or saline may be administered in a double-blinded manner. Instruction control groups are informed that only saline is administered as part of standardized procedures. In the subsequent *Experience Phase*, thermal pain stimulation intensities are surreptitiously increased in the negative experience groups to create a clearly discernable experience of amplified pain, whereas intensities remain unaltered in the experience control groups. Two *Test Phases* are accomplished, comprising the identical pain stimulation intensities as during *Baseline*. To test short-term effects of expectancy manipulations, the first test phase is accomplished on study day 1 (*Test-1 Phase*). To explore the persistence of effects, another test phase is accomplished 1 week later (*Test-2 Phase*), yet without any of the salient elements of the treatment context (i.e., there is no i.v. and no interaction with the study physician). In all pain stimulation phases, different facets of visceral and somatic pain perception are acquired, along with questionnaires and ratings, psychophysiological recordings, and saliva and blood sampling at various time points (see section 2.5 for details on measures). Note that in order to minimize circadian effects, all experimental testing is accomplished between 13:00 and 17:00 h, with identical starting times for study day 1 and 2 for each participant. Participants are instructed to abstain from physical exercise on the study day, and to omit food and drink (other than water) within 90 min of the scheduled arrival to the laboratory. They are also instructed not to apply body lotion on the abdomen given application of electrodes on the skin.

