As primary outcomes, changes in perceived pain intensity and pain unpleasantness will be assessed based on testing for interaction effects and planned group comparisons regarding changes from *Baseline* to the *Test-1 Phase* within each pain modality (study aims 2 and 3). Group differences between pain modalities will be tested based on analysis of delta scores (i.e., changes in visceral > somatic pain responses) (aim 4). Secondary pain-related outcome measures, also tested based on changes from *Baseline* to the *Test-1 Phase* within and between pain modalities, include pain-related expectations (study aim 1), pain recall, and desire to avoid pain. Secondary outcomes related to fear and stress are measured using behavioral, neuroendocrine, and psychophysiological responses, relevant particularly to study aim 6. Responses to pain-predictive cues, i.e., change in cue valence rating and in skin conductance responses, are tested for each pain modality and based on the same experimental phases as for pain-related measures. For neuroendocrine measures, we plan to compare groups with respect to changes from Baseline to subsequent sampling time points. Similarly, group comparisons of differences in heart rate variability and electrogastrogram will be based on analyses of the entire pain stimulation phases (for details, see section 2.4.2). Please note that analyses are planned in two separate steps. Initially, analyses of results of study day 1 will be accomplished. In a second step, analyses comparing data from study day 1 and day 2 (i.e., *Test-1 Phase* vs. *Test-2 Phase*) will be accomplished to explore the possible persistence of nocebo effects over time upon re-exposure to pain stimuli 1 week later (study aim 5). Mediation analyses will be accomplished for aim 1.

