
Limitations and potential pitfalls are equally important to consider. Firstly, while all participants are truthfully informed that the purpose of the study is to elucidate psychobiological mechanisms underlying changes in visceral compared to somatic pain perception upon repeated painful experiences, the study procedures of consent form A (i.e., negative instruction groups) involve a deception. To induce negative treatment-related expectations, participants are informed that they have a 50% chance of receiving either a pronociceptive drug or saline, mimicking clinical treatment scenarios characterized by uncertainty regarding symptom worsening or the occurrence of side effects or adverse events, such as in clinical trials. In reality, herein the probability of receiving saline is 100%. The administration of saline and the scientific justification for providing different instructions to experimental groups will be disclosed after the conclusion of the study, at which time participants will have the opportunity to withdraw their data. While a comprehensive discussion of ethical considerations is beyond the scope herein, the use of deception is not unequivocal, requires justification, and rightfully constitutes an issue of critical debate. There exist different solutions, such as open-label placebos [e.g., (87)], with limited applicability for nocebo research, and authorized consent [e.g., (88)]. A comprehensive work focused on ethical considerations specifically pertaining to nocebo effects is provided herein (89). Secondly, while interindividual variability is a highly relevant aspect to consider, it could at the same time hamper the detection of small effects. The sample size with a goal of *N* = 30 per experimental group was determined based on a prior power calculation and is consistent with (or even larger than) similar experimental work on visceral pain modulation [e.g., (40)] and the broader field [reviewed in (90)]. While the inclusion of diverse and complementary secondary outcome measures at different levels (behavioral, psychophysiological, brain) is consistent with sustainability goals in scientific research and will allow exploratory analyses of diverse study aims, multiple tests and comparisons will be accomplished. This comprehensive study protocol provides readers with maximal transparency, however, there is a risk of potential inflation of *p*-values and false positive results, and findings will have to be interpreted with due caution, requiring replication in independent samples and/or settings. Thirdly, normal changes in perceptual responses to repeated visceral vs. somatic stimuli may differ between modalities as well as between individuals, as suggested by our previous work in similar paradigms. Careful calibration and matching accomplished herein to overcome this challenge may not fully prevent this, with a habituation to cutaneous thermal pain stimuli over time constituting the most likely pitfall. This will be quantifiable in the “Control–Control” group, and of course statistically-controlled for, but analyses directly focusing on differences between pain modalities induced by expectancy manipulations will nevertheless have to overcome this variability. As we cannot with certainty exclude that spontaneous changes in perception occurring independent of our expectancy manipulations interfere with their impact in a modality-specific manner, we will conduct initial analyses within each pain modality separately, i.e., without including pain modality as a repeated factor. Dedicated analyses will be accomplished to elucidate differences between modalities, e.g., using delta scores on the modality difference, as previously accomplished [e.g., (41)]. Finally, limitations arise from the fact that the study is conducted in a tightly-screened sample of relatively young healthy adults. We will recruit men and women, offering opportunities to explore effects of sex/gender, especially within predictor analyses (aim 6). Regarding planned group analyses (e.g., for aims 2–4), (sub)sample sizes are likely too small for any firm conclusions regarding effects of sex/gender, yet exploratory analyses can be accomplished and are interesting given that females and males may differ with respect to the generation of expectancies by suggestions and conditioning processes, respectively (91). Mitigating possible gender-related confounding remains a challenge in experimental research, especially in studies involving visceral pain stimuli posing feasibility restrictions for larger samples that would provide adequate statistical power for detecting sex differences. We and others have previously accomplished some dedicated research on this important subject in the context of visceral pain and visceral pain modulation [e.g., (31, 92–94), as recently reviewed in (9)]. Overall, volunteers herein will not be representative of diverse age, cultural, and ethnic groups, and certainly not of vulnerable individuals or even patients with DGBI and multiple comorbidities. As a complex psychosocial phenomenon, expectancy effects in psychosocial treatment contexts are modulated by societal, cultural, and numerous individual factors, which we will only partially be able to capture and interrogate herein. This is particularly relevant for analyses aiming to address the putative contribution of trait- and state measures relevant to stress and anxiety. While it is tempting to speculate that interactions between stress and negative expectancy effects — whether induced by suggestions or conditioning—could be increased in patients, the translation from healthy individuals tested in experimental laboratory settings to clinical populations is far from unequivocal. Clearly, it is a challenging yet indispensable future research task to elucidate mediators and moderators of placebo and nocebo responses in patients experiencing chronic visceral pain in order to delineate the putative role of stress in nocebo effects in laboratory research, everyday clinical practice as well as in clinical trials.

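### Section 2.1 states 0.90 power at N = 96 for d = 0.4, but the calculation that most plausibly gives 96 assumes group differences of about 0.8 to 1.1 change-score SD

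*Protocol article*

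**What the plan says.** Section 2.1 of the protocol article describes a G*Power calculation for "interaction effects in a repeated measure ANOVA with the factors time and group". It assumes an "effect size of *d* = 0.4 for interaction effects, *α* = 0.05, and 1-β = 0.90, the number of volunteers is *N* = 96". The target is then raised to 120, 30 in each of four groups, "To account for possible exclusions or drop-out and to allow stratified recruitment of male and female volunteers". The article does not define d. It gives no Cohen's f, no correlation between phases, and no number of groups or measurements entered.

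Section 2.2 sets the primary analysis as "testing for interaction effects and planned group comparisons regarding changes from *Baseline* to the *Test-1 Phase* within each pain modality", with instruction and experience as separate between-group factors. Section 3.1.3 names aim 3, the combination of instruction and experience, as the most crucial aspect of the study. Section 3.2 then defends the group size by saying that it "was determined based on a prior power calculation and is consistent with (or even larger than) similar experimental work" on visceral pain modulation.

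**The concern.** A reader takes d as a standardized difference between two means, and so takes section 2.1 to promise 0.90 power for a group difference of 0.4 SD. Power for a repeated-measures ANOVA is computed from Cohen's f, the spread of the means across groups. Setting f = d/2 is exact for two equal groups. It does not carry over to a pattern of four group means, where the same f corresponds to a larger difference between the extreme groups.

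The 0.90 also belongs to one test. The primary analysis includes planned group comparisons, and aim 3 depends on the instruction-by-experience contrast. Both have less power than the omnibus test at the effect it was sized for. At stake is how null results are read: someone relying on sections 2.1 and 3.2 could treat a non-significant planned comparison as evidence against a 0.4 SD nocebo effect.

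**Working it through.** **Inputs.** From the article: alpha 0.05, power 0.90, N = 96 and recruitment goal 120 (section 2.1); k = 4 groups, equal allocation, so 24 or 30 per group; m = 2 phases, Baseline and Test-1, for the primary outcome (section 2.2). Assumed, because not stated: f = d/2 = 0.2, correlation ρ = 0.5, sphericity.

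**Reproducing 96.** For the within-between interaction, λ = f²·N·m/(1−ρ), df1 = (k−1)(m−1), df2 = (N−k)(m−1). At N = 96, λ = 0.04 × 96 × 2/0.5 = 15.36 with df 3 and 92, and power is 0.912. At N = 92 power is 0.898, so 96 is the smallest multiple of four that reaches 0.90. At N = 120 power is 0.964.

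This set of inputs is not the only one. With f = 0.2, four groups, four phases and ρ = 0.25, N = 96 also comes out (0.901; 0.885 at N = 92). The two-phase reading is the more plausible because the primary comparison uses two phases.

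**What f = 0.2 means for change scores.** With m = 2 the test is a one-way ANOVA on change with f_change = f·√(m/(1−ρ)) = 0.2 × √4 = 0.40. So the four group mean changes have an SD of 0.4 change-score SD. The largest group difference a depends on the pattern:

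- (0, 0, a, a), one factor works: SD = a/2, so a = 0.80
- (0, 0, 0, a), only Neg-Neg reacts: SD = a·√3/4, so a = 0.92
- (0, a/2, a/2, a), equal single effects that add up: SD = a/√8, so a = 1.13

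Exactly 0.90 power at N = 96 needs f_change = 0.392, which gives a = 0.78, 0.91 and 1.11.

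**Power if d = 0.4 is a group difference in change-score SDs** (the same as raw SDs at ρ = 0.5). For a = 0.4 the omnibus λ is N × 0.04, N × 0.03 or N × 0.02 for the three patterns. For a pair, λ = n·d²/2. For a 1-df factor-by-time main effect, λ = N·d²/4. For the instruction-by-experience contrast (a difference of differences of 0.4), λ = n·d²/4. Here n is the group size.

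| Test | λ at N = 96 | Power, N = 96 | Power, N = 120 |
|---|---|---|---|
| Omnibus, one factor works | 3.84 | 0.33 | 0.41 |
| Omnibus, only Neg-Neg | 2.88 | 0.25 | 0.32 |
| Omnibus, additive | 1.92 | 0.18 | 0.22 |
| Planned pair | 1.92 | 0.27 | 0.33 |
| Factor-by-time main effect | 3.84 | 0.49 | 0.58 |
| Instruction × experience | 0.96 | 0.16 | 0.19 |

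**Power if d = 0.4 is in raw-rating SDs.** The difference in change-score SDs is 0.4/√(2(1−ρ)), which is 0.516 at ρ = 0.7 and 0.632 at ρ = 0.8. At N = 96:

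| Test | ρ = 0.7 | ρ = 0.8 |
|---|---|---|
| Omnibus (range over patterns) | 0.28–0.53 | 0.41–0.72 |
| Planned pair | 0.42 | 0.57 |
| Factor-by-time main effect | 0.71 | 0.87 |
| Instruction × experience | 0.24 | 0.33 |

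At N = 120 the factor-by-time test has 0.80 and 0.93.

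**Difference detectable with 0.90 power** (change-score SDs, 24 then 30 per group): planned pair 0.96 and 0.85; factor-by-time main effect 0.67 and 0.60; instruction × experience contrast 1.34 and 1.19.

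**The case against.** The strongest reply is that nothing has been miscalculated. N = 96 comes out once f = d/2 and ρ = 0.5 are entered. That stands: a reader might infer an arithmetic error, and the document does not support that.

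A reader might also infer that 96 can arise from one set of inputs only. It cannot be pinned down that far, because four phases with ρ = 0.25 give the same total. The inputs used above are an inference.

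A third temptation is to say flatly that a true d of 0.4 has 18% to 33% power. That range is for the omnibus test at N = 96 with d read in change-score SDs. It leaves out the factor-by-time test (0.49), the instruction-by-experience contrast (0.16) and the recruitment goal of 120. It also fails if d is in raw SDs and the phases are highly correlated: at ρ = 0.8 and N = 120 the factor-by-time test exceeds 0.90.

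A journal article may leave software inputs to the full protocol, so their absence alone is no fault. Section 3.2 does warn that variability may obscure small effects, asks for caution and replication, and also appeals to the size of similar studies. Section 3.1.3 concedes that effects in the single-manipulation groups cannot be estimated beforehand. These points soften the consequence. They do not repair the printed pairing of d = 0.4 with 0.90 power, which section 3.2 relies on without qualification.

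**Conclusion.** The point holds as a misstated effect size. On the most plausible reconstruction, 0.90 power at N = 96 applies to the omnibus time-by-group test when the extreme groups differ by about 0.8 to 1.1 change-score SD, which is 2 to 2.8 times the printed 0.4. For a 0.4 change-score SD group difference, none of the tests examined comes near 0.90. The best is the factor-by-time main effect, at 0.49 with 96 and 0.58 with 120. The aim 3 contrast has 0.16 and 0.19.

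This rests on two assumptions: that f = 0.2, two phases and ρ = 0.5 were entered, and that d is in change-score SDs (or in raw SDs at ρ = 0.5). A raw-SD reading with a higher correlation gives more power, but the article states no such correlation. A reader might conclude that the trial must be enlarged. The document does not require that, because the fault lies in what the stated power is said to cover.

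**What to change.** Keep N = 120.

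- **Section 2.1:** replace d = 0.4 with the effect size actually entered (f, number of groups, number of measurements, correlation), confirmed by the sponsor from its own G*Power record, and give the group difference it implies. If the inputs were f = 0.2, four groups, two phases and ρ = 0.5, that is a spread of 0.4 change-score SD and a largest difference of about 0.8 to 1.1 SD.
- **Section 2.1:** add the differences detectable with 0.90 power at 24 to 30 per group: about 0.96 to 0.85 SD for a planned pair, 0.67 to 0.60 SD for a factor-by-time main effect, and 1.34 to 1.19 SD for the instruction-by-experience contrast.
- **Section 3.2:** cite these figures in place of the unqualified power calculation, and state that null planned comparisons will be interpreted from their confidence intervals.

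The cost is wording only, with no extra participants and no change of analysis. The downside is that the stated power becomes less favourable.
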